### Data collection and analysis for impact measurement

For the impact survey, in the stratified random sample 10 clusters (enumeration areas) in each of the intervention and control districts, trained fieldworkers will conduct the interviews and take finger prick blood samples for rapid HIV screening testing. The interviewers will go house to house, starting from a random point, until they reach the target number of interviews; there will be no sub-sampling within the cluster.

The fieldworkers will administer the questionnaire in the Setswana language. The questionnaire will collect information about the secondary outcomes of use of government support programs, gender violence and sexual behaviours described above, including intermediate variables based on the CASCADA model of behaviour change. Specific questions will include those we have used and validated in previous surveys in the region in 2007 [65–67] and 2008 [68].

The interviewers will use Open Data Kit (ODK) Collect [69] on Android tablets to record responses. Field supervisors will check data on the tablets and upload the records to ODK Aggregate hosted on a server in Botswana.

The fieldworkers will take the finger prick blood samples in the household setting, using single-use safety lancets, with a blade that retracts immediately into the hub after use, to eliminate the theoretical risk of blood exposure while taking the sample.

#### Statistical methods

We will adopt an intention-to-treat principle for measuring primary outcomes with district as the unit of analysis. The primary analysis will treat the two groups of districts as a parallel design, and will use a two-sample t-test to compare the HIV prevalence rate of young women aged 15–29 years in the five first wave (intervention) and the five second wave (control) districts. Since the impact assessment in the first wave will coincide with the baseline in the second wave, the analysis will be able to ignore temporal effects.

Secondary analysis will compare HIV and gender violence related knowledge, attitudes and behaviours in young women and men between intervention and non-intervention districts, adjusting for clustering. Adjusted analysis using regression techniques will investigate the residual impact of key baseline characteristics on the outcomes. We will examine the residuals for model assumptions and chi-squared test of goodness-of-fit. Analysis will rely on CIETmap software [70] which provides a windows interface with the statistical programming language R.

We will summarize district demographics and outcome variables (both primary and secondary) using descriptive measures: mean (standard deviation) or range (minimum-maximum) for continuous variables and number (percent) for categorical variables.

Sensitivity analysis will examine correlated outcomes using generalized estimating equations, assuming intervention as a fixed effect, district as clustering variable and an exchangeable or unstructured covariance structure to model correlation of participants within a district. Planned subgroup analysis will focus on subgroups of young women with different exposures [71]. Age is a core issue in gender violence and HIV incidence. A history of sexual abuse is likely to affect responses across a range of themes. Variables on use of alcohol and other substances may be informative, as well as employment or educational status and exposure to workshops in the intervention districts.

We will use multiple-imputation to deal with missing data [72]. All statistical tests will be two-sided at the 0.05 level of significance. The Bonferroni method will adjust the level of significance for testing for secondary outcomes to keep the overall level at alpha = 0.05. We will express results as effect or odds ratio/relative risk reduction for binary outcomes, standard errors, corresponding two-sided 95% confidence intervals and associated *p*-values.

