### Sample size

The intervention package will potentially affect all young women in each intervention district. However, the impact assessment will rely on a cluster random sample of communities drawn from the recent census. There are thus two quite different domains – the domain of intervention (*all* young women in the intervention districts) and the domain of the survey (the *sample* of villages or clusters that will provide evidence of the impact on young women in the district) within which we will include all young women with no sub-sampling within the cluster.

Sample size calculations for the survey used a calculator developed by Taylor and colleagues [64]. The HIV prevalence in Botswana control clusters in the 2012 impact assessment was 23% among women aged 15–29 years ([name], personal communication). In the Botswana AIDS Impact Survey of 2013, the HIV prevalence among women aged 15–49 years was 28.2% [39]. Since districts are the unit of randomization, intervention and analysis, starting from 23% (range 17–28%, k = 0.119), 650 women per district in five districts in each arm would detect a reduction to 17.25% (25% reduction in HIV) at the 5% significance level with 80% power. In the unpublished three-country study, the combined interventions in Botswana produced a reduction in HIV of around 50% ([name], personal communication); these sample size calculations therefore allow for some inefficiency in taking the interventions to scale.

We will select a stratified random sample of 10 clusters (enumeration areas) from each of the five intervention districts, and 10 from the control (next wave of intervention) districts. From each cluster we will interview and test for HIV (rapid screening testing of finger prick blood) around 100 young people aged 15–29 years (at least 65 of them women). The sample will include around 5000 people from intervention districts and 5000 from non-intervention districts. To achieve these numbers, the overall sample size *invited to participate* in the survey will need to be around 7500 to allow for absentees and those who decline to participate. Some 13.1% of young women contacted in the 2012 survey in the three countries declined to participate, and a further 14% were absent at the times the interviewer could visit ([name], personal communication).

Secondary outcomes (such as gender violence, unsafe sexual behaviours) are more common occurrences and the power to detect these is correspondingly greater.

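### The primary t-test compares crude district HIV prevalence and makes no use of age; a two-stage age adjustment would be a cheap gain in precision

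*Protocol article*

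**What the plan says.** All places are in the protocol article.

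- **Statistical methods, primary analysis.** It follows an "intention-to-treat principle for measuring primary outcomes with district as the unit of analysis" and "will use a two-sample t-test to compare the HIV prevalence rate of young women aged 15–29 years". No covariate is named.
- **Statistical methods, age.** The plan states that "Age is a core issue in gender violence and HIV incidence". The sentence stands among the planned subgroup analyses.
- **Statistical methods, other models.** A regression-adjusted analysis of baseline characteristics is in the secondary-analysis paragraph and lists no covariates. The sensitivity analysis by generalized estimating equations names intervention as its only effect.
- **Allocation.** Districts are stratified by HIV prevalence and by development and economic status, the latter including the urban/rural make-up. Age structure is not a factor.
- **Data collection and analysis for impact measurement.** "The interviewers will go house to house, starting from a random point, until they reach the target number of interviews". No age quota is described.
- **Sample size.** The calculation runs "starting from 23% (range 17–28%, k = 0.119" and concludes that "650 women per district in five districts in each arm would detect a reduction to 17.25% (25% reduction in HIV". The power claimed for this is 80%, with alpha set to 5%.

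**The concern.** HIV infection is lifelong, so prevalence between 15 and 29 should rise with age. A district whose sampled women are older will tend to show a higher crude prevalence for that reason alone. The age mix of each sample depends on the local population and on who is found at home, and with five districts per arm some imbalance in mean age is likely by chance.

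That variation enters the primary comparison as noise. A woman's own age cannot be altered by the intervention, unlike schooling or employment, so it is a safe adjustment variable. What is at stake is some power in a trial with only ten analysis units, and the ability to say in advance how an age imbalance would be handled if one appears.

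**Working it through.** **Inputs from the Sample size and Statistical methods sections.** Control prevalence p0 = 0.23; intervention prevalence p1 = 0.1725; difference 0.0575; k = 0.119; n = 650 women per district; c = 5 districts per arm; two-sided 5%.

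**Step 1: reproduce the plan's figure.**

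- Sampling variance: 0.23×0.77/650 + 0.1725×0.8275/650 = 0.000492.
- Between-district variance: 0.119² × (0.23² + 0.1725²) = 0.001170.
- Total V = 0.001663, of which 0.001170/0.001663 = 70% is between districts.
- Cluster formula: c = 1 + (1.96 + 0.84)² × V / 0.0575² = 4.95, which rounds up to 5. Power with c − 1 = 4 is 80.5%.
- Planned t-test: SE = √(V/5) = 1.82 points; noncentrality 5.75/1.82 = 3.15; power on 8 degrees of freedom is 78.8%.

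The stated 80% therefore reproduces to within about a point. The quoted range gives (0.28 − 0.17)/4/0.23 = 0.1196, close to k. This suggests, but does not prove, that k describes crude variation with any age component still in it.

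**Step 2: assumptions, not in the document.** Prevalence rises linearly by b = 1.5, 2.0 or 2.6 points per year of age. The SD of district mean age is s = 0.3, 0.5 or 0.7 years. Ages are roughly uniform over 15–29, with variance (15² − 1)/12 = 18.67.

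**Step 3: effect of removing age.**

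- Age-driven SD of district prevalence: b × s.
- Share of between-district variance explained: (b×s)² / (0.119×23)², where 0.119×23 = 2.74 points.
- Share of within-district variance explained: b² × 18.67 / (0.23×0.77), with b as a proportion. This is 2.4%, 4.2% or 7.1% for the three slopes.
- SD of the chance shift in the arm difference: b × s × √(2/5).

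Example with b = 2.0 and s = 0.5: the shares are 13.3% and 4.2%. V becomes 0.000492×0.958 + 0.001170×0.867 = 0.001486, noncentrality is 0.0575/√(0.001486/5) = 3.34, and power is 83%.

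| Points per year | SD of mean age (years) | Between-district variance explained | SD of chance shift (points) | Power after adjustment |
|---|---|---|---|---|
| 1.5 | 0.3 | 2.7% | 0.28 | 80% |
| 1.5 | 0.5 | 7.5% | 0.47 | 81% |
| 1.5 | 0.7 | 14.7% | 0.66 | 83% |
| 2.0 | 0.3 | 4.8% | 0.38 | 81% |
| 2.0 | 0.5 | 13.3% | 0.63 | 83% |
| 2.0 | 0.7 | 26.2% | 0.89 | 87% |
| 2.6 | 0.3 | 8.1% | 0.49 | 82% |
| 2.6 | 0.5 | 22.6% | 0.82 | 86% |
| 2.6 | 0.7 | 44.2% | 1.15 | 92% |

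The median is 83%, about 4 points above the crude 78.8%.

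**Step 4: simulation check.** Five of these cells were simulated with 3,000 runs each. Crude against adjusted power was 79.3/80.0% (1.5, 0.3), 79.1/83.3% (2.0, 0.5), 80.1/85.8% (2.6, 0.5), 80.4/88.5% (2.0, 0.7) and 79.1/91.9% (2.6, 0.7). Under no effect the adjusted test rejected in 4.6–5.7% of runs.

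**The case against.** The strongest reply is that nothing here is wrong. A district-level t-test is unbiased and valid under randomisation, its stated power reproduces, and a simple primary analysis is a defensible choice with ten units. That stands.

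A reader might infer that a chance age difference could mimic or hide an effect over and above what the test allows for. The document does not support that. The chance shift is part of the between-district variation that k and the 1.82-point SE are meant to cover, so counting it again would be double counting.

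Four further points have force:

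- The urban/rural element of the stratification may already balance part of the age mix. That would shrink the chance shift, and the gain would overlap with any gain from adding stratum terms.
- An adjusted analysis is foreseen, and the covariate list may sit in an analysis plan not shown. It is secondary, however, and leaves the primary estimate as it is.
- The 92% figure needs age mix alone to explain 44% of between-district variance. A generic 25% cut in total variance would give 88.9%, but nothing in the document supports that figure, and it exceeds the cut in eight of the nine cells.
- That age is recorded for each woman is inferred from the eligibility range and the age subgroup; it is not stated outright.

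A reader might also suspect that the programme changes which women are at home in year five, so that age mix differs by arm for more than chance reasons. The document gives no evidence on this.

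**Conclusion.** The point holds as a cheap improvement. The plan fixes a crude primary comparison, and none of its other analyses brings age into the primary estimate. The consequence is lost precision and exposure to chance age imbalance. It is not bias, not an inflated error rate and not a mistake in the sample size.

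The likely gain is about 4 points of power, within 80–92% across the assumed grid against 78.8% crude. It is nearly nil if district age mixes are alike. The size rests wholly on the assumed age slope and spread of mean age. The conclusion that age is unused in the primary test rests only on the text.

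**What to change.** Before unblinding, prespecify the primary comparison in two stages:

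1. Fit a logistic regression of HIV status on age to women from all ten districts together, with no arm term. For each district take observed minus expected prevalence.
2. Apply the planned two-sample t-test to the ten district residuals, with district as the unit and 8 degrees of freedom.

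Use age only at this stage, not schooling, work or other characteristics that the intervention may change. Report the crude t-test as a sensitivity analysis.

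The cost is a sentence in the Statistical methods section and a few lines of R, with no new data if age is recorded as the subgroup plan implies. Stage 1 ignores arm, so it fits the planned blinded analysis. Adjusting at individual level spends no district degrees of freedom, whereas a district-level age covariate would spend one. The downside is that the headline estimate becomes age-standardised rather than raw, and the gain may be small.

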### Allocation

Central randomization of districts will stratify by two factors (1) HIV prevalence (above or below the national average), using results of the fourth Botswana AIDS Impact Survey (BAIS IV) [39] and (2) development and economic status including proportions of urban and rural communities.

An epidemiologist not involved in the fieldwork will centrally randomize districts using an online random number generator, with allocation concealment until commencement of each wave. We will unmask the first wave districts immediately, and the second wave in year 5. Local intervention activities will be obvious to residents in the intervention sites. Knowledge of *future* intervention status may become clear to residents of the second wave at the time of their baseline study, in year 5. Some secondary outcomes (particularly conscious knowledge) could be influenced by knowledge of intervention status. Other indicators like a reduction in gender violence or HIV status would be less susceptible to this bias.

Interviewers in the impact survey will not include intervention fieldworkers and, as far as possible, they will be kept unaware if the communities in which they are interviewing are in intervention or non-intervention districts. The principal analysis will be undertaken blind of intervention status, using only group labels for each district.

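### Randomisation is stratified by district HIV prevalence and development status, but the primary t-test ignores the strata: valid, probably conservative, and cheap to improve with one term

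*Protocol article*

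**What the plan says.** On allocation, the protocol article (Allocation) states: "Central randomization of districts will stratify by two factors (1) HIV prevalence (above or below the national average"), using BAIS IV results. The second factor is "2) development and economic status including proportions of urban and rural communities". It does not say how many levels the second factor has.

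On analysis (Statistical methods), the article adopts an "intention-to-treat principle for measuring primary outcomes with district as the unit of analysis" and "will use a two-sample t-test to compare the HIV prevalence rate of young women aged 15–29 years" between five first-wave and five second-wave districts. No stratum term is mentioned. The sensitivity analysis by generalised estimating equations lists intervention and district, again without a stratum term. The paragraph on secondary analysis adds: "Adjusted analysis using regression techniques will investigate the residual impact of key baseline characteristics on the outcomes". It does not name the stratification factors. The article also says: "All statistical tests will be two-sided at the 0.05 level of significance".

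On sample size, the article gives "starting from 23% (range 17–28%, k = 0.119), 650 women per district in five districts in each arm", which "would detect a reduction to 17.25% (25% reduction in HIV) at the 5% significance level with 80% power".

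**The concern.** Stratified allocation tends to balance the strata between arms, so differences between strata largely drop out of the arm contrast. An unstratified t-test still counts those differences in its error term. If the strata predict the outcome, the standard error is then too large, the interval too wide, and the true error rate below the stated 5%. One stratification factor is an earlier measurement of district HIV prevalence, so some predictive value is plausible.

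With five districts per arm and most of the variance lying between districts, part of the benefit of stratifying may be left unused in the primary result. A real reduction in HIV would then be reported with a wider interval and a larger p-value than the design supports.

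**Working it through.** **Inputs (Sample size section).** Control prevalence p0 = 0.23; intervention p1 = 0.1725; difference d = 0.0575; m = 650 women per district; c = 5 districts per arm; between-district coefficient of variation k = 0.119; two-sided alpha 0.05. **Assumption:** R, the share of between-district variance that the prevalence term explains, is not given, so a range is shown.

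**1. The plan's own figure.** Variance per pair of districts:

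V = p0(1−p0)/m + p1(1−p1)/m + k²(p0² + p1²) = 0.000272 + 0.000220 + 0.001170 = 0.001663

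The between-district part is 0.001170/0.001663 = 70%. The unmatched cluster formula gives c = 1 + (1.960 + 0.842)² × V/d² = 1 + 3.95 = 4.95, rounded up to 5. Power is 80.5% by the normal formula with c − 1 = 4, and 78.8% by the noncentral t on 8 degrees of freedom (df). The stated 80% therefore reproduces for an unstratified comparison. The value of k is also close to (0.28 − 0.17)/4/0.23 = 0.1196, an overall spread with no credit taken for stratification.

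**2. Effect of a balanced stratum on precision.** The t-test works with a standard error of about √(V/5) = 1.82 percentage points, so a half-width of 2.306 × 1.82 = 4.2 points. With B = 0.001170, the adjusted standard error is √((V − R·B)/5):
- R = 0.25: 1.66 points; half-width 2.365 × 1.66 = 3.9 points (7 df).
- R = 0.50: 1.47 points; half-width 2.365 × 1.47 = 3.5 points (7 df).

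**3. Error rate and power.** Simulation of 5 against 5 districts, with true district prevalence equal to the arm's prevalence × (1 + k·E), E being part prevalence term (share R) and part random, and binomial sampling of 650 women. Binary means the above/below stratum, balanced 2 and 3 in each arm. For the continuous covariate, the error rate is for median-split stratified allocation with the fifth district falling at random; adjusted power runs from chance imbalance to that median-split allocation. The four-strata column is by noncentral t on 5 df, assuming two development levels.

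| R | Type I of unadjusted test: binary / continuous | Power, unadjusted | Power adjusted, binary (7 df) | Power adjusted, continuous (7 df) | Power adjusted, four strata (5 df) |
|---|---|---|---|---|---|
| 0 | 5% / 5% | 79% | 77% | 72–75% | 71% |
| 0.25 | 3.0% / about 4% | 79% | 84% | 79–82% | 79% |
| 0.50 | 1.4% / about 3% | 79–80% | 91% | 87–90% | 87% |

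The adjusted tests hold 5% throughout. If the odd fifth district falls at random between the two levels of the binary stratum, the unadjusted test runs at 3.3% (R = 0.25) and 1.9% (R = 0.50), and adjusted power is 84% and 91%.

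**4. Break-even.** Adjustment gains power once R exceeds about 0.06 for the balanced binary stratum, about 0.13 to 0.25 for a continuous covariate, and about 0.24 for all four strata.

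**The case against.** The strongest defence is that nothing here is invalid. The unadjusted test errs only towards caution, so it carries no added false-positive risk. The article already plans regression adjustment, and naming the covariates is commonly left to the analysis plan. The share of variance explained is not in the documents. The BAIS IV figures that the article quotes cover wider groups (18 months to 64 years for incidence, women 15–49 for prevalence) than the endpoint group of women 15–29, and the precision of the district figures is not given. With five districts per arm, exact balance on two factors is not assured. A single prevalence term also leaves out the development factor. All of this stands, and it limits how far the point can be pressed. It does not remove it: the article fixes the primary test, and the planned adjustment sits under secondary analysis without naming the factors that governed allocation.

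Three stronger readings are tempting and not supported:
- A reader might infer that the trial needs adjustment to reach its power. It does not; the stated 80% was computed without it.
- A reader might arrive at about 70% power for the planned test. That follows from applying the control-arm spread (0.119 × 0.23) in both arms. The calculation that reproduces the article applies k to each arm's own prevalence and gives 79%.
- A reader might take the cost of any single covariate to be just one degree of freedom. For a continuous covariate in ten districts, chance imbalance adds variance, and the loss is 4 to 7 points if it predicts nothing.

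**Conclusion.** The mismatch between stratified allocation and unstratified primary analysis is real. The primary test is valid and conservative to the extent that the strata predict endline prevalence. Under the article's own variance model, the unadjusted test runs at about 3.0 to 4.1% if a single prevalence term explains 25% of between-district variance, and at about 1.4 to 3.0% if it explains 50%. One-term adjustment then gives power of about 82 to 84% and 90 to 91%, against 79%. In each range the more favourable power belongs to the balanced binary stratum and the other to a continuous covariate under median-split allocation; a continuous covariate left to chance imbalance would give 79% and 87%.

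The conclusion rests on the assumed share explained and on reasonable balance of the prevalence stratum between the two waves. The direction is plausible because the stratifier is earlier HIV prevalence, but the size is unknown. This is a cheap improvement, not an error that threatens the trial's conclusions.

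**What to change.** Before unblinding, specify the primary analysis as a district-level linear regression of HIV prevalence in women aged 15–29 on arm plus one BAIS IV prevalence term, tested on 7 df. The preferred term is the above/below-average stratum already used for randomisation: it needs no new data and has the lowest break-even. Report the unadjusted two-sample t-test as supportive. Do not enter all four strata as indicators; that leaves 5 df and gains power only if they explain more than about a quarter of between-district variance.

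The cost is about one sentence and one degree of freedom (critical t from 2.31 to 2.36). If the term explains nothing, power falls by about 2 points with the balanced binary stratum (79% to 77%), or by 4 to 7 points with a continuous covariate. No change to fieldwork or sample size is needed.

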##### For impact surveys

Young women and young men aged 15–29 years in 10 clusters (random selection of enumeration areas from the recent census) in each of five intervention and five non-intervention districts.

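### The GEE sensitivity analysis allows an unstructured correlation that cannot be estimated from 10 districts; its small-sample inference and the clustering level for secondary outcomes should also be fixed in the text

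*Protocol article*

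**What the plan says.** All references are to the protocol article; no separate analysis plan is shown.

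- **Primary analysis (Statistical methods).** The plan follows an "intention-to-treat principle for measuring primary outcomes with district as the unit of analysis" and "will use a two-sample t-test to compare the HIV prevalence rate of young women aged 15–29 years" in five intervention and five control districts.
- **Sensitivity analysis (Statistical methods).** "Sensitivity analysis will examine correlated outcomes using generalized estimating equations, assuming intervention as a fixed effect", with "district as clustering variable and an exchangeable or unstructured covariance structure to model correlation of participants within a district". No variance estimator, small-sample correction or reference distribution is named.
- **Secondary analysis (Statistical methods).** Knowledge, attitudes and behaviours are compared "between intervention and non-intervention districts, adjusting for clustering". The level of clustering is not named.
- **What a cluster is.** The survey eligibility section places respondents "in 10 clusters (random selection of enumeration areas from the recent census"), and the Sample size and data collection sections use the word in the same way. Elsewhere the district is the cluster: Sample size says "Since districts are the unit of randomization, intervention and analysis", the Trial design and Informed consent sections describe cluster randomisation of districts, and the GEE sentence names district.
- **Size.** "650 women per district in five districts in each arm would detect a reduction to 17.25"%, from 23% with k = 0.119.

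**The concern.** The three parts differ in strength.

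1. An unstructured working correlation gives every pair of positions in a cluster its own parameter. That suits a few repeated measurements at fixed times. Here the members of a cluster are several hundred people found house to house. The third woman in one district does not correspond to the third woman in another, so the parameters have no meaning, and there are far too few districts to estimate them.

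2. With five clusters per arm, the uncorrected GEE sandwich variance is too small, and a normal reference ignores the few degrees of freedom. Used that way, the sensitivity analysis could look significant where the t-test does not, and could be quoted against it.

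3. If the secondary comparisons were adjusted at enumeration-area level only, the variance between districts, which are the randomised units, would be left out. Secondary findings could then be false positives.

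**Working it through.** **Inputs from the article:** 5 districts per arm; 650 women per district; 10 enumeration areas per district with at least 65 women each; prevalence 23% against 17.25%; k = 0.119; two-sided 5%; 80% power.

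**Step 1. Reproduce the plan's own figure.** The formula for an unmatched cluster trial is c = 1 + (1.96 + 0.84)² × [p₁q₁/m + p₂q₂/m + k²(p₁² + p₂²)] / (p₁ − p₂)².
- Bracket: 0.000272 + 0.000220 + 0.000749 + 0.000421 = 0.001663.
- c = 1 + 7.849 × 0.001663 / 0.003306 = 4.95, so 5 districts per arm.
- Power with 5 per arm is 80.5% by this formula and 78.8% by the noncentral t on 8 df.

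The stated design is reproduced, with the district as its unit.

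**Step 2. Unstructured correlation.** The number of parameters is m(m − 1)/2. For 650 women it is 650 × 649 / 2 = 210,925. For about 1,000 people of both sexes per district it is 1,000 × 999 / 2 = 499,500. Only 10 districts inform them.

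**Step 3. Exchangeable GEE on 10 districts.** With equal cluster sizes, the uncorrected sandwich variance of an arm mean is Σ(pᵢ − p̄)²/25 = (4/5) × s²/5. The Wald z is therefore √(5/4) times the two-sample t (exact on the identity scale, approximate on the logit scale). A Kauermann-Carroll-type correction multiplies the variance by 5/4, and Mancl-DeRouen by 25/16. The true error is the tail of t on 8 df beyond the rescaled critical value:

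| Variance | Reference | Effective cut-off on t₈ | True two-sided error |
|---|---|---|---|
| Uncorrected | z | 1.96 × √0.8 = 1.753 | 11.8% |
| Uncorrected | t₈ | 2.306 × √0.8 = 2.063 | 7.3% |
| × 5/4 | z | 1.960 | 8.6% |
| × 5/4 | t₈ | 2.306 | 5.0% |
| × 25/16 | z | 1.96 × √1.25 = 2.191 | 6.0% |
| × 25/16 | t₈ | 2.306 × √1.25 = 2.578 | 3.3% |

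Null simulations agree (prevalence 23%, k = 0.119, 40,000 runs per setting). The uncorrected z gave 11.7–12.0%, the × 5/4 variance with t₈ gave 4.9–5.1%, and the planned t-test gave 4.8–5.1%. An actual exchangeable GEE fit (2,000 runs) gave 11.2% with default robust inference.

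**Step 4. Clustering on enumeration area only.** Take e as the between-area coefficient of variation within a district. It is not in the article, so it is an assumption. Per district:
- variance as an area-level analysis sees it: [pq/65 + (kp)² + (ep)²]/10;
- true variance: (kp)² + [pq/65 + (ep)²]/10.

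With e = 0 these are 0.000347 and 0.001022, a ratio of 2.94. The error is P(|Z| > 1.96/√2.94 = 1.143) = 25.3%.

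| Assumed e | Ratio | Error by formula | Error by simulation |
|---|---|---|---|
| 0 | 2.94 | 25.3% | 27.1% |
| 0.10 | 2.68 | 23.2% | 25.1% |
| 0.25 | 1.99 | 16.5% | 17.6% |
| 0.40 | 1.56 | 11.7% | 12.7% |

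The value k = 0.119 is for HIV prevalence in women. The article gives no k for the secondary outcomes. With an assumed k of 0.06 and e = 0.25, the simulated error is 9.0%.

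**The case against.** The strongest reply concerns what the article does not say. A reader might infer that the plan commits to uncorrected robust inference and so more than doubles its false-positive rate. The text does not support that. It gives the fixed effect, the clustering variable and the working correlation, and stops. The variance correction for a sensitivity model is commonly left to an analysis plan, which is not shown. This objection stands, so the 11–12% is conditional.

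A reader might also infer that cluster always means enumeration area. That is not so either. The Trial design, Sample size, Statistical methods and Informed consent sections all treat the district as the cluster, and district is the only clustering variable named in Statistical methods. The enumeration-area reading is the less natural one. What remains is an unnamed level in one sentence. In Statistical methods the district as unit of analysis is tied to primary outcomes, and the survey sections use the same word for another unit.

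It can be said that an option that cannot be fitted yields no p-value and so does no harm. That is right about error rates, but the article still offers a choice in which only one branch works.

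The planned Bonferroni adjustment would not repair the secondary comparisons. As an illustration, assume six tests, one for each behaviour listed under Outcomes, at 0.05/6 = 0.0083 each. The true per-test error would be about 4.6% with uncorrected GEE, and about 12.4% with area-only clustering at k = 0.119 and e = 0.

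**Conclusion.** The unstructured option is wrong as written and needs no assumption to show it: 210,925 correlations without meaning, from 10 districts.

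The other two parts are clarifications whose size depends on how the gap is filled. Uncorrected sandwich errors with a normal reference would give about 11–12% instead of 5%. This assumes near-equal district sizes, as planned. Clustering the secondary outcomes on enumeration area alone would give roughly 12–27%, if the HIV value of k carried over and the between-area coefficient of variation lay between 0 and 0.40. Neither assumption comes from the article, and a smaller k gives a smaller excess.

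The primary two-sample t-test on district prevalences keeps about 5% error and is not in question. What is exposed is the sensitivity analysis, and any secondary comparison analysed in one of these ways.

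**What to change.** Make three edits in Statistical methods:

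1. Delete the unstructured alternative and keep exchangeable.
2. State that GEE inference uses a small-sample-corrected sandwich variance with a t reference on 8 df. A Kauermann-Carroll-type correction gives about 5%. Mancl-DeRouen with t on 8 df is conservative here, at about 3%, so the choice should be named in advance.
3. For secondary outcomes, state that the adjustment is for clustering by district, with enumeration area at most as a level nested within it.

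The cost is about two sentences and no change to data collection. The downside is wider intervals: with the × 5/4 correction, the half-width is 2.306 × √1.25 / 1.96 = 1.32 times that of the uncorrected z interval.
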